### **Specific Aim 3: To measure and compare ED operational processes and crowding when targeted and nontargeted rapid HIV screening strategies are fully-integrated into ED care**

**Hypothesis 3:** Enhanced targeted rapid HIV screening is not associated with: **(a)** longer patient waiting times; **(b)** longer patient length of stay times; **(c)** longer patient ED boarding times; **(d)** larger proportion of patients who leave prior to completing medical evaluation; or **(e)** greater overall crowding when compared to traditional targeted rapid HIV screening or nontargeted rapid HIV screening.

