Five specific metrics of ED patient throughput will be measured in this aim. All five measures are commonly thought to represent ED processes of care and crowding. The first metric, patient waiting time, will be defined as the time from initiation of medical screening by the screening nurse to the time the patient is assigned a bed in the ED. The second metric, patient length of stay, will be defined as the time from when the patient is assigned a bed in the ED to the time of discharge or, for those admitted to the hospital, the time an inpatient bed is requested by a physician. The third metric, patient boarding time, will be defined as the time from when an inpatient bed is requested to the time the patient leaves the ED for that bed. The fourth metric, proportion of patients who leave before completion of evaluation, will be defined as the proportion of all patients who either leave before being placed in a treatment room or leave before completion of their evaluation. The fifth metric, Emergency Department Work Index (EDWIN) or the National ED Overcrowding Score (NEDOCS), are global or composite crowding metrics and are defined as:

$$\text{EDWIN} = \sum n_i t_i / N_a (B_T - B_A),$$

where  $n_i$  = the number of patients present in the ED by triage category ( $i$ );  $t_i$  = the acuity category (defined using an ordinal scale from 1 to 5, 1 being the most acute and 5 being the least acute);  $N_a$  = the number of physicians on duty at a given time;  $B_T$  = the total number of beds available in the ED; and  $B_A$  = the number of admitted patients waiting for inpatient bed assignment in the ED. The EDWIN metric can range from 0 to infinity, and a previous validation study demonstrated median EDWIN scores of 1.1 (IQR: 0.8 – 1.6), 1.6 (IQR: 1.2 – 1.9), and 1.8 (IQR: 1.4 – 2.5) during non-busy, average, and busy ED time periods, or

$$\text{NEDOCS} = -20 + 85.8(\text{total ED patients} \div \text{total ED beds}) + 600(\text{boarded patients} \div \text{total hospital beds}) + 13.4(\text{number of ventilated patients in the ED}) + 0.93(\text{longest boarder time in hours}) + 5.64(\text{longest time for patient waiting in hours})$$

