where 0 – 20 is considered “not busy”, 21 – 60 considered “busy”, 61 – 100 considered “very busy”, 101 – 140 considered “crowded”, 141 – 180 considered “dangerous”, and 181 or greater considered “disaster”. EDWIN and NEDOCS have been compared head-to-head and have both been shown to be valid and comparable metrics for quantifying ED crowding.

Values for each of the four basic time metrics will be collected real-time for all patients enrolled into the study using electronic patient tracking systems. Patients who register for evaluation in each ED on a daily basis include time stamps related to initiation of medical screening, ED bed assignment, patient discharge or admission to the hospital and, if admitted to the hospital, inpatient bed assignment. Because EDWIN and NEDOCS rely on point-in-time sampling and at the level of the ED, it is not feasible to measure their variables on a continuous, real-time basis. However, we will calculate the fifth ED metric, either EDWIN or NEDOCS, at the time each patient begins medical screening and when he or she is discharged. The difference between these data will be used as a covariate in the analyses for this aim as described below.

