Process metric variables for all enrolled patients will be compared between study arms. Because the time and EDWIN or NEDOCs metrics are continuous, they will be reported as means with SDs or medians with IQRs. Bivariate analyses will be used to estimate statistical differences between each process metric and the three HIV screening interventions. Because we propose measuring five ED process metrics, we have defined statistical significance for this part of the analyses to be a Bonferroni-adjusted p-value <0.01. Also, hierarchical multivariable linear regression analyses will also be used to estimate associations between each of the interventions and continuous process metrics, while accounting for clustering at the institution level and adjusting for overall ED crowding as measured by the difference in either EDWIN or NEDOCs for the duration of the patient's visit. If necessary, continuous data will be transformed and multiple imputation will be used in instances where data are missing. The primary unit of analysis will be patient visits.

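### The adjusted Aim 3 regression conditions on the change in ED crowding over the visit, a partly post-randomisation variable timed by the visit's own length, and can bias the arm effect on ED times

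*Protocol*

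**What the plan says.** Hypothesis 3 (Protocol section 1, Specific Aim 3) states that enhanced targeted screening is not associated with longer waiting, length-of-stay or boarding times, with more patients leaving early, or, under (e), with "greater overall crowding when compared to traditional targeted rapid HIV screening or nontargeted rapid HIV screening".

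Section 4.F (Outcome Measures, Specific Aim 3) defines five metrics. Waiting time starts when the nurse begins medical screening. For patients sent home, length of stay is "the time from when the patient is assigned a bed in the ED to the time of discharge"; for admitted patients it ends at the bed request, and boarding time runs from there until the patient leaves the ED. The fifth metric is EDWIN or NEDOCS. That score is to be calculated "at the time each patient begins medical screening and when he or she is discharged", and then: "The difference between these data will be used as a covariate in the analyses for this aim".

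Section 4.H (Analytic Plan, Specific Aim 3) plans two analyses. The first is unadjusted: "Bivariate analyses will be used to estimate statistical differences between each process metric and the three HIV screening interventions". Because there are five metrics, "we have defined statistical significance for this part of the analyses to be a Bonferroni-adjusted p-value <0.01". The second is a hierarchical linear regression of the continuous metrics, clustered by institution and "adjusting for overall ED crowding as measured by the difference in either EDWIN or NEDOCs for the duration of the patient's visit". The protocol does not say which of the two decides Hypothesis 3.

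**The concern.** Individual patients are randomised at triage, so confounding between arms is already dealt with by design. A covariate in the arm comparison can add precision, but for that it should be fixed before allocation can affect it. The crowding change does not meet this condition, for three reasons.

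- Its second reading comes after randomisation.
- The time of that reading is set by the visit. A patient who waits or stays longer is read at a later point in the ED's day, so the covariate depends on the outcome even if the patient has no influence on crowding.
- Crowding is both the fifth outcome and the adjuster. Section 4.H treats the crowding score as a continuous metric and regresses the continuous metrics on arm. Taken literally, the crowding model adjusts crowding for its own change.

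If screening in one arm delays patients, part of that delay may be absorbed by the covariate. Hypothesis 3 asserts no association, so attenuation would work in the hypothesis's favour.

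**Working it through.** **The plan's own figure.** Five metrics at an overall 0.05 give 0.05 / 5 = 0.01, which matches section 4.H. The protocol gives no effect size, standard deviation or correlation for Aim 3. Every input below is therefore an assumption, used only to show what the covariate can do.

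**Algebra.** Let A be the arm, Y the ED time, τ the true delay and D the change in crowding. Suppose D depends on A only through Y, with slope b. Regressing Y on A and D gives

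adjusted effect = τ(1 − b·g), with g = Cov(Y, D | A) / Var(D | A).

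*No common cause of Y and D.* Write D = bY + u. Then b·g = b²Var(Y|A) / [b²Var(Y|A) + Var(u)] = ρ², where ρ is the within-arm correlation of Y and D. The share kept is 1 − ρ², whatever the sign of b:

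| Assumed ρ | 0.1 | 0.2 | 0.3 | 0.5 | 0.7 |
|---|---|---|---|---|---|
| Share of τ kept | 0.99 | 0.96 | 0.91 | 0.75 | 0.51 |

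*With a common cause.* Suppose a busy ED at arrival lengthens the stay and crowding then falls back. Take b = 0.005 per minute, 60 minutes of stay per SD of starting crowding, a fall-back of 1.5 per SD, and residual SDs of 100 minutes for Y and 0.6 for D.

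- Var(Y|A) = 60² + 100² = 13,600
- Cov(Y, D|A) = 0.005 × 13,600 − 1.5 × 60 = −22
- Var(D|A) = 0.005² × 13,600 − 2 × 0.005 × 1.5 × 60 + 1.5² + 0.6² = 0.34 − 0.90 + 2.25 + 0.36 = 2.05
- Factor = 1 − 0.005 × (−22 / 2.05) = 1.05, slightly away from zero

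If b = 0, the factor is 1 and there is no bias.

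**Simulation** (1,000,000 visits per setting, true delay 10 minutes). Estimates are in minutes. In the last four rows crowding follows a fixed 24-hour cycle that the patient cannot influence; the paired values are without and with an effect of time-of-day crowding on stay.

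| Setting | Unadjusted | Adjusted for change | Adjusted for start value |
|---|---|---|---|
| No common cause, ρ = 0.64 | 9.99 | 5.98 | 9.99 |
| No common cause, ρ = −0.64 | 10.55 | 6.20 | 10.55 |
| Common cause, stronger reversion | 9.82 | 9.45 | 9.89 |
| Common cause, weaker reversion | 10.00 | 10.11 | 10.09 |
| Daily cycle, arrivals round the clock | 10.11; 10.05 | 10.11; 9.91 | 10.11; 10.03 |
| Daily cycle, arrivals 7–13 h | 10.04; 9.66 | 9.90; 9.82 | 10.04; 9.69 |
| Daily cycle, arrivals 12–20 h | 9.83; 10.19 | 8.81; 9.09 | 9.83; 10.18 |
| Daily cycle, arrivals 15–22 h | 9.96; 10.25 | 8.49; 8.63 | 9.96; 10.20 |

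In each setting the unadjusted and start-value estimates agree within 0.1 minute, and across settings they lie between 9.7 and 10.6; that spread is simulation error. In the daily-cycle rows, adjusting for the change shifts the estimate by +0.16 to about −1.6 minutes.

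**The case against.** The strongest reply is that the unadjusted comparison comes first in section 4.H, followed by the 0.01 threshold, and that the regression is an addition to it. The unadjusted comparison contains no crowding term, so a reader who infers that every Aim 3 result is biased goes further than the protocol allows. This stands. It is weakened only because the protocol does not say which analysis decides the hypothesis. The linear regression also does not cover the proportion leaving early, which is not continuous.

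A reader might also infer that the bias always runs toward no effect. That holds only where ED time and crowding change share no common cause. Crowding at arrival is an obvious common cause, and with it the bias can nearly vanish or reverse slightly.

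Size is open too. Screening runs 24 hours a day (section 4.D), and with arrivals round the clock the daily-cycle shift was 0 to −0.14 minutes; the larger losses needed afternoon and evening arrivals. In the no-common-cause model the standard error also shrinks, by √(1 − ρ²), so the test statistic falls by that same factor: √0.96 = 0.98 at ρ = 0.2, a loss of about 2%.

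It is tempting to argue that a patient's own delay feeds the score directly, since NEDOCS includes the longest wait and longest boarding time. This is nearly empty. Both are maxima across the ED, and the patient's own wait is over by discharge. Even for the longest boarder, 10 extra minutes add 0.93 × 10/60 = 0.16 points on a scale whose top band starts at 181.

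Finally, the protocol allows either index but does not say that the two scales will share one coefficient, so mixed scales are only a conditional worry.

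None of this justifies the covariate. It limits the direction, size and reach of the harm.

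**Conclusion.** The flaw is real but confined to the adjusted regression of a secondary aim. Sections 4.F and 4.H fix a covariate that is partly post-randomisation, whose second reading is timed by the length of the visit, and that is built from an Aim 3 outcome. It can bias the arm effect on waiting time, length of stay or boarding time, most plausibly toward zero and so toward Hypothesis 3.

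How much is unknown, because the protocol gives no correlation between ED time and crowding change. With no common cause, the loss is 1% at an assumed ρ of 0.1, 9% at 0.3 and 25% at 0.5; with a common cause it may be negligible or slightly reversed. Adjusting the crowding outcome for its own change is unsound whatever the correlation.

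The unadjusted comparisons by arm at p<0.01 and the Aim 1 primary risk ratio are unaffected. Severity is minor to moderate.

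**What to change.** - In section 4.F (Specific Aim 3) and section 4.H (Specific Aim 3), replace the difference, now worded as "as measured by the difference in either EDWIN or NEDOCs", with the EDWIN or NEDOCS value at the start of medical screening. Do not use the discharge value or the change as a covariate.
- State that the crowding outcome is not adjusted for its own change.
- State that the unadjusted comparison by arm decides Hypothesis 3 and that the regression is supportive.
- If sites use different indices, standardise the score within site before pooling.

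The cost is a few sentences. The start-of-screening value is already to be calculated for every patient, so no new data are needed and the sample size does not change.

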### **G. Data Management**

For all aims, data will be electronically transferred or manually entered into a secured electronic database (Microsoft SQL, Microsoft Corporation, Redmond, WA) or spreadsheet (Microsoft Excel, Microsoft Corporation, Redmond, WA). The Denver site will serve as the Data Coordinating Center (DCC) and data from the three non-Denver institutions will be transferred to the DCC using a secure file transfer protocol (SFTP). Data will be transferred, concatenated, and cleaned using SAS (SAS Institute, Inc., Cary, NC), and statistical analyses will be performed using SAS Version 9.3, Stata Version 12 (Stata Corporation,

College Station, TX), or their most current versions (for all Specific Aims), and Microsoft Excel (for Specific Aim 2). See Data Protection section below for additional details related to data acquisition, cleaning, and transfer to the DCC.

## **H. Analytic Plan**

All statistical analyses will be conducted by the Principal Investigator and independently confirmed by the study's biostatistician blinded to study allocation. Final analyses will be performed after cleaning and locking of the dataset. Although no formal interim analyses are planned, the study team may perform preliminary analyses for purposes of presentation at scientific meetings; these instances, if they occur, will be explicitly described as preliminary and qualified as such.

### Specific Aim 1

Descriptive analyses will be performed for all variables. Continuous data will be reported as means with standard deviations (SDs) or medians with interquartile ranges (IQRs), depending on whether they are normally distributed or non-normally distributed, respectively; additionally, categorical data will be reported as proportions or percentages with 95% confidence intervals (CIs). Bivariate statistical tests (e.g., Student's t-test or Wilcoxon rank sum test for two-group parametric or non-parametric comparisons, ANOVA or Kruskal-Wallis test for three-group parametric or non-parametric comparisons, and chi-square test or Fisher's exact test) will be used to compare variables between study groups. Patient-level data will be reported for demographics. Otherwise, patient-visit data will be reported given the relatively large degree of recidivism to EDs; as such, the primary unit of analysis will be patient visits.

All analyses will be performed using the intention-to-treat principle and no interim analyses are planned given the "pragmatic" trial approach and minimal risk to subjects. Given the randomized controlled trial design, the primary comparison will include unadjusted risk ratios (RRs) for newly-identified HIV infection (primary outcome) with 95% CIs, specifically comparing enhanced targeted HIV screening to nontargeted HIV screening (the primary hypothesis of this study). Statistical significance for the primary analysis will be defined as  $<0.05$  based on two-tailed statistical testing, which includes a lower 95% confidence limit of  $>1.0$ .

Secondary comparisons will include unadjusted RRs for: (1) traditional targeted HIV screening to nontargeted HIV screening (the secondary hypothesis of this aim); and (2) the composite secondary outcome, newly-diagnosed and repeat-diagnosed HIV infection for both hypotheses. Additionally, HIV prevalence, including overall prevalence and test prevalence, and 95% CIs will be reported for each study group, and institution-specific subgroup analyses will be performed as well as hierarchical multivariable binary Poisson regression to account for clustering at the level of the institution and repeat visits at the level of the patient, while adjusting for age, sex, race/ethnicity, primary language, pay status, and acuity level. Results of these latter analyses will be reported as adjusted RRs with 95% CIs. Finally, additional comparative analyses will be performed, including: (1) absolute numbers of new HIV diagnoses; (2) proportions identified early in the disease course (defined by an initial CD4  $>350$  cells/ $\mu$ L) and late in the disease course (defined by an initial CD4  $<200$  cells/ $\mu$ L); (3) proportions successfully linked into care; (4) patient characteristics stratified by those who do and do not agree to HIV testing after screening; and (5) frequency of unscheduled medical visits, use of antiretroviral therapy, treatment for opportunistic infections, hospitalizations, and mortality over the 12 months following initial diagnosis. Any other analyses will be considered exploratory and described as post-hoc.

### Specific Aim 2

All cost and time-motion data will be manually entered and analyses will be performed using Microsoft Excel (Microsoft Corporation, Redmond, WA). Double data entry will be performed to minimize data entry error. Total direct costs will be calculated and compared between interventions. As each intervention will not extend beyond 12-months, it will be unnecessary to discount costs, although all costs will be annualized. We will use the number of newly-diagnosed HIV-infected patients, the primary outcome from Specific Aim 1, as an intermediate outcome for this aim. The scope of this aim is not to perform decision analyses or disease transition-state modeling, but instead to systematically collect valid cost data and to report cost effectiveness of the 3 screening approaches using an intermediate outcome. Results of this aim will inform future modeling, including from a society perspective, by our team. Total direct costs per patient identified with HIV infection at the institutional level will be reported as CERs and incremental CERs, or the additional costs per patient identified with HIV infection beyond those incurred by nontargeted screening. Because underlying distributions of cost data are often skewed, we will report bootstrap 95% CIs for each CER and ICER. Finally, sensitivity analyses will be performed to determine the effects of individual parameter ranges on the results.

### Specific Aim 3

Process metric variables for all enrolled patients will be compared between study arms. Because the time and EDWIN or NEDOCs metrics are continuous, they will be reported as means with SDs or medians with IQRs. Bivariate analyses will be used to estimate statistical differences between each process metric and the three HIV screening interventions. Because we propose measuring five ED process metrics, we have defined statistical significance for this part of the analyses to be a Bonferroni-adjusted p-value <0.01. Also, hierarchical multivariable linear regression analyses will also be used to estimate associations between each of the interventions and continuous process metrics, while accounting for clustering at the institution level and adjusting for overall ED crowding as measured by the difference in either EDWIN or NEDOCs for the duration of the patient's visit. If necessary, continuous data will be transformed and multiple imputation will be used in instances where data are missing. The primary unit of analysis will be patient visits.

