During this aim, we will collect the following data elements for all eligible patients: (1) patient visit information (unique patient identifier, acuity level, mode of arrival, and date/time of visit); (2) demographics (age, sex, race/ethnicity, primary language); (3) payer information (commercial, Medicare, Medicaid, self, or state-sponsored); (4) details of randomization, including the intervention assigned and results of risk screening, if applicable; (5) whether a patient was offered, accepted, and completed rapid HIV testing; (6) results from all rapid HIV tests; and for all patients with at least one reactive HIV test; (7) results of confirmatory test results, additional behavioral risk information as collected during post-test counseling, initial CD4 counts and viral loads, whether they were successfully linked into care, and details of follow-up care and disease progression. Data from (1) through (5) will be collected prospectively using methods developed and validated in Denver from each institution's electronic screening, patient tracking, and laboratory reporting systems. Our study team has extensive experience interfacing with such systems and obtaining large amounts of valid patient-level data. Data from (6) and (7) will be retrospectively obtained using trained personnel and structured procedures. See **Data Dictionary, "Positive Patient Risk Information Data Collection Instrument"** and **"Longitudinal Data Collection Instrument" / "Limited Longitudinal Data Collection Instrument"** in the **Appendix**.

Specific Aim 2

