## **F. Outcome Measures**

### Specific Aim 1

Confirmed newly-diagnosed HIV infection will serve as our primary outcome. In anticipation of testing patients with previously diagnosed HIV infection (i.e., repeat diagnoses), our secondary outcome will include a composite of new diagnoses and repeat diagnoses.

Although confirmed newly-diagnosed HIV infection will serve as the primary outcome for this study, we believe important secondary effectiveness evaluations include disease state at the time of diagnosis as well as a longer-term evaluation of access to care, disease progression, and treatment. Therefore, additional outcomes will include behavioral risk information, CD4 count (cells/ $\mu$ L) and viral load (copies/mL) at the time of diagnosis, and successful linkage into care (defined as completion of an initial HIV clinic visit). Details of follow-up care and disease progression for a period of one year following diagnosis will also be collected, including the number of scheduled and unscheduled medical care visits, whether antiretroviral therapy and treatment for opportunistic infections were initiated, the number of hospitalizations, and mortality.

### Specific Aim 2

Programmatic costs associated with implementation of targeted and nontargeted rapid HIV screening strategies when fully-integrated into ED settings will be measured. We will estimate program costs using a simple cost allocation method that sums fixed and variable costs for program implementation. Components of costs by intervention arm will include: start-up, personnel, tests, supplies, and equipment. In order to estimate personnel-related costs by arm, time-motion data will be collected during randomly-selected time periods of the trial at each site (including different times of day and weekends). Personnel time spent per patient will be monetized by position title-specific median salary data from the Bureau of Labor Statistics for the respective metropolitan statistical area. Total programmatic costs, costs per person tested, and cost per HIV case detected will be compared by intervention arm. Differences across sites will be explored in sensitivity analyses. Uncertainty in cost estimates will be estimated using bootstrapping resampling methods.

### Specific Aim 3

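### Early-stage, late-stage and linkage proportions are most naturally read as shares of diagnosed patients, a group the screening arm itself selects, so comparing them between arms is not a randomised comparison

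*Protocol*

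**What the plan says.** Protocol section 4.H, Specific Aim 1, ranks its analyses. The unadjusted risk ratio for new diagnosis comes first, then the secondary risk ratios, prevalences, subgroups and adjusted models. The last group opens: "Finally, additional comparative analyses will be performed, including: (1) absolute numbers of new HIV diagnoses". Items (2) and (3) of that list are "proportions identified early in the disease course", with the matching late proportion, and "proportions successfully linked into care". The section then declares anything not listed to be exploratory and post hoc.

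Other parts of the protocol bear on how items (2) and (3) are read:

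- Section 4.E (Specific Aim 1) collects initial CD4 count, viral load and linkage "for all patients with at least one reactive HIV test".
- Section 4.F says that "important secondary effectiveness evaluations include disease state at the time of diagnosis", and defines linkage as attending a first HIV clinic appointment.
- Section 4.D makes the test offer depend on the arm: everyone eligible in the nontargeted arm, and only those flagged as higher risk by the respective tool in the two targeted arms.
- Section 4.H also states "All analyses will be performed using the intention-to-treat principle", makes the patient visit the primary unit of analysis, and lists bivariate tests that "will be used to compare variables between study groups".

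**The concern.** A CD4 stage or a linkage status exists only once a patient has been diagnosed. A proportion early, late or linked is therefore most naturally a share of the diagnosed. Who is diagnosed is what the intervention changes and what the primary outcome measures. The diagnosed groups in the three arms are selected by different rules after randomisation, so randomisation does not make them comparable.

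What is at stake is the reading of these outcomes. An arm that finds the same early cases plus some further, more advanced ones shows a lower early share, although it loses nothing on early detection and gains overall. An arm that finds fewer cases can show a higher early share. The plan lists no analysis of early, late or linked diagnoses per randomised visit. If one were added later, the closing sentence of that paragraph would make it post hoc.

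**Working it through.** **Inputs**

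- Nontargeted arm: 25% test completion, 0.3% test prevalence (section 4.I).
- Enhanced targeted arm: 5% test completion, 2% test prevalence (section 4.I).
- Visits: up to 120,000 in all (section 5.C), allocated 1:1:1, so up to 120,000 / 3 = 40,000 per arm. This is a ceiling.
- CD4 mix: not in the protocol. It is assumed below and varied.

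**Step 1: expected diagnoses.** Yield per visit is 0.25 × 0.003 = 0.075% (nontargeted) and 0.05 × 0.02 = 0.100% (enhanced). The ratio is 0.100 / 0.075 = 1.33, which reproduces the point estimate in section 4.I. The confidence interval stated there is not used here. At 40,000 visits per arm the counts are 40,000 × 0.00075 = 30 and 40,000 × 0.001 = 40.

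**Step 2: how the two measures relate.** Let D be diagnoses and E early diagnoses, with equal visits per arm (1 = enhanced, 0 = nontargeted). Then

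share ratio = (E1/D1) / (E0/D0) = (E1/E0) / (D1/D0) = RR of early diagnosis per visit / RR of diagnosis per visit.

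Under the planning assumptions the divisor is 1.33. Any true RR of early diagnosis between 1.00 and 1.33 then appears as a share ratio between 0.75 and 1.00: a deficit, or no difference, where enhanced screening is equal or better per visit.

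**Step 3: illustration.** Assume 15 of the 30 nontargeted diagnoses are early, and vary how many of the 10 extra enhanced diagnoses are early.

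| Early among the extra 10 | Early share, nontargeted | Early share, enhanced | Share ratio | RR per randomised visit |
|---|---|---|---|---|
| 0 | 15/30 = 50% | 15/40 = 37.5% | 0.75 | 15/15 = 1.00 |
| 2.5 | 50% | 17.5/40 = 43.8% | 0.88 | 17.5/15 = 1.17 |
| 5 | 50% | 20/40 = 50% | 1.00 | 20/15 = 1.33 |
| 10 | 50% | 25/40 = 62.5% | 1.25 | 25/15 = 1.67 |

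The first row does not depend on the assumed 50%. With 30% early the shares are 9/30 = 30% and 9/40 = 22.5%; with 60% they are 18/30 = 60% and 18/40 = 45%. The ratio is 0.75 each time.

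**Step 4: precision in the first row.** Per-visit RR = (15/40,000) / (15/40,000) = 1.00. The SE of log RR is √(1/15 + 1/15) = 0.365, so the 95% CI is exp(±1.96 × 0.365) = 0.49 to 2.05. For the shares, the difference is 37.5% − 50% = −12.5 points. Its SE is √(0.5 × 0.5/30 + 0.375 × 0.625/40) = 0.119, so the 95% CI is about −36 to +11 points, with p about 0.30.

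**Step 5: the opposite direction.** Take hypothetical arms of equal size, one with 12 early of 20 diagnosed and the other with 16 of 32. The share ratio is 60% / 50% = 1.20, but the RR per visit is 12/16 = 0.75.

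**Step 6: linkage.** If 80% of the diagnosed are linked in both arms (assumed), the shares are equal, yet the linked counts are 0.8 × 30 = 24 and 0.8 × 40 = 32, a ratio of 1.33. The same ratio holds for any common linkage share.

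**The case against.** The strongest case on the other side has five parts.

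- **The denominator is inferred.** Section 4.H makes the visit the primary unit, so the wording could mean visits at which an early case was found, and a separate analysis plan might settle it. This stands as a caveat. The data-collection and outcome sections still point to diagnosed patients, and the clause making unlisted analyses post hoc is a reason to settle it in the protocol.
- **Intention-to-treat is not breached.** A reader might infer that items (2) and (3) contradict the intention-to-treat statement. The document does not support that: tabulating stage by assigned arm moves nobody between arms. The problem is conditioning on a later event, which affects what the contrast means.
- **These are low-tier outcomes.** Both Aim 1 hypotheses concern new diagnoses, and stage and linkage carry no success criterion. This stands, although section 4.F calls the evaluations important.
- **Item (1) already gives absolute numbers.** With counts shown, a reader can see 15 and 15. This stands in part. Item (1) covers all new diagnoses and not early, late or linked ones, and no risk ratio for those is planned.
- **Shares among the diagnosed answer a fair question, and the example is constructed.** Both are true. Stage at diagnosis and linkage among the diagnosed are useful description, so barring any comparison of them would go too far. A reader might also infer that the trial would conclude that enhanced screening finds cases later. At these counts the interval of about −36 to +11 points would not support that conclusion.

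**Conclusion.** The point holds in a limited form. On the natural reading, items (2) and (3) compare arms within a subset that the intervention determines, so those contrasts are not randomised and cannot alone rank the strategies on timeliness of diagnosis or linkage. Under the plan's own yields the share ratio equals the per-visit RR divided by 1.33, so equal early detection would appear as 50% against 37.5%.

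This rests on three assumptions: the inferred denominator, the CD4 mix, and 40,000 visits per arm. The last sets the counts but not the factor of 1.33. The effect is confined to additional outcomes. A reader might infer that the primary comparison is compromised; it is not, because new diagnosis is analysed by assigned arm over patient visits.

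**What to change.** In section 4.H, Specific Aim 1, replace items (2) and (3) with three outcomes defined for every randomised visit: new diagnosis with initial CD4 above 350, new diagnosis with initial CD4 below 200, and new diagnosis linked to care. Compare arms by risk ratio with 95% CI over all randomised visits. Keep the shares among diagnosed patients, always with numerator and denominator, labelled as descriptive and non-randomised. Show by arm how many newly diagnosed patients have no CD4 result, since they cannot be classed as early or late.

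The cost is wording and a few table rows; the data are already collected. The per-visit ratios will be imprecise (15 against 15 gives 0.49 to 2.05), and the text should say so.
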